## Study aim and objectives

The aim of the study is to assess the impact of a 16-week supervised group exercise intervention, combined with physical activity recommendations delivered via a booklet, on overall physical activity, physical functioning, and quality of life among breast cancer survivors. The primary outcome includes aerobic capacity (assessed via directly measured peak oxygen consumption, or VO_2_)_._ Secondary outcomes are physical activity (assessed via accelerometry and questionnaire), physical functioning (assessed via muscle strength, balance, and agility), self-reported quality of life, fatigue, presence of lymphedema, body composition, immune function, adherence to physical activity guidelines, and perceptions of self-image.

Additionally, we will investigate whether supervised aspects of the intervention enhanced participants’ motivation for physical activity and exercise, and whether changes in motivation are linked to adherence to exercise program and higher levels of physical activity overall.

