### Participant randomization and group allocation

Prior to group randomization, a researcher blinded to the future group allocation will classify participants into quartiles based on their peak VO_2_ values. Subsequently, participants from each quartile will be randomly assigned with a 1:1 allocation ratio to 1) supervised group: canoeing and physical activity recommendations (*n* = 18), or 2) unsupervised group: physical activity recommendations (*n* = 18). Following randomization, participants in both groups will be invited to a meeting at the School of Physical Education and Sport at the University of Sao Paulo, where the researcher and the physician will communicate the importance of an active lifestyle and the benefits of physical activity for people living with cancer. In addition, participants will be introduced to the physical activity recommendations booklet (based on WHO guidelines) produced by ICESP. The researcher and physician will outline the goal of achieving physical activity guidelines (i.e., 150 min of moderate-to-vigorous physical activity/exercise per week). Participants will be advised that recommendations can be achieved through separate bouts of activity, such as 50 min per day on three non-consecutive days each week, or 30 min 5 days a week. Following, the physician, who will be blinded to the allocation, will leave the room and the researcher will inform each participant which intervention group they have been allocated to. For participants in the supervised group (canoeing and physical activity recommendations), canoeing training schedules are explained, whereas for those participants allocated in the unsupervised group, best days and times for telephone calls will be arranged so the researcher can remotely investigate whether this group is reaching physical activity recommendations.

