### Statistical analysis

#### Power calculation and sample size

Sample size calculations were performed based on the predicted maximum oxygen consumption (VO_2_—ml/kg min) of patients with breast cancer [95] using G-Power Software (Version 3.1.9.2). Sample size was carried out a priori, assuming a power (1 − *β* error) of .90 and assuming *α* error of .05. The calculation was based on an F test with analysis of variance by repeated measures and between- and within-group effects. To eliminate possible sample size bias, the Hedges *g* calculation was used. The effect size used in the calculation was based on the work of Courneya et al. [95] considering the maximum oxygen consumption (VO_2_—ml/kg min) of patients with breast cancer. A pre- to post-test correlation value of 0.50 was assumed. Power calculations indicated a sample size of *n* = 15 participants per group were required to achieve a power = .90 and *α* error = .05. To account for participant drop-out during the intervention, the sample size was increased by 20% to *n* = 18 participants per group. Therefore, we aim to recruit a total sample of *n* = 36 participants to the study.

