#### Data analysis

The data analyst will receive the raw data coded for participant names and group allocation after completion of data collection. Group allocation will be unblinded after termination of data analyses. The Shapiro–Wilk and Levene’s tests will be used to determine normality and variance equality, respectively, and non-normal scale data will be log transformed. If the transformation does not produce a normal distribution, residual analyses will be performed to test if influential points change the interpretation of the results. If interpretations change, these points will be manually removed. Linear mixed models having group and time as fixed factors and participants as a random factor will be performed for each dependent variable [maximal aerobic capacity (VO_2_ max), daily physical activity, and adherence to physical activity guidelines (assessed via accelerometry and questionnaire), physical functioning (assessed via muscle strength, balance, and agility), self-reported quality of life, fatigue and perceptions of self-image (assessed via specific validated questionnaires), presence of lymphedema, and body composition and immune function]. Baseline differences in outcomes will be examined by independent *t*-test. An analysis of covariance (ANCOVA) will be implemented including the baseline variable as a covariate, group as a fixed factor, and participants as a random factor, in case of differences in baseline values between groups. An intention-to-treat analysis will also be performed in case of a high incidence of missing values, using linear mixed models; the first analysis will be performed removing the missing values, while the second analysis will be performed incorporating the missing data points to determine the impact of missing values in the overall results [96]. Whenever a significant F-value is obtained, a post hoc test with Tukey’s adjustment will be performed. Ordinal data will also be analyzed using mixed models having group and time as fixed factors, and participants as random factor. Nominal data will be compared using chi-square distributions and significance will be determined by residual analyses (< − 2 or > 2).

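### Baseline adjustment depends on a baseline t-test that stratification on peak VO2 practically prevents from firing; the primary test stays valid but is conservative and loses a few points of power

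*Protocol article*

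**What the plan says.** All references are to the protocol article.

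- **Primary outcome (Study aim and objectives):** "The primary outcome includes aerobic capacity (assessed via directly measured peak oxygen consumption". The Assessments section schedules it before and after the 16 weeks only.
- **Allocation (Participant randomization and group allocation):** before randomisation a researcher "will classify participants into quartiles based on their peak" VO2, and then "participants from each quartile will be randomly assigned with a 1:1 allocation ratio", with 18 women per arm.
- **Default model (Data analysis):** a linear mixed model for every outcome, with group and time fixed and participant random. No group-by-time term is named.
- **Conditional switch (Data analysis):** "Baseline differences in outcomes will be examined by independent" t-test. An ANCOVA with the baseline value as covariate, group fixed and participant random is used "in case of differences in baseline values between groups".
- **Planning correlation (Power calculation and sample size):** "A pre- to post-test correlation value of 0.50 was assumed".

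No section adjusts for baseline peak VO2, or for its quartiles, whatever the data show.

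**The concern.** A t-test between randomised arms does not tell the analyst whether adjustment is worthwhile. What matters is how strongly baseline predicts outcome, and for peak VO2 the plan itself assumes that it does. Letting that t-test choose the model has two consequences.

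For the primary outcome the switch conflicts with the design. Balancing baseline peak VO2 by quartile keeps its t-test from becoming significant, so the ANCOVA clause is in effect dead text there. The test is then run without the variable used to randomise, and its standard error is that of an unstratified trial.

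For outcomes unrelated to VO2, chance decides which of two models is reported.

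There is also a smaller fault. In an ANCOVA with one post value per woman, a participant random effect cannot be separated from the residual.

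**Working it through.** **Inputs.** From the protocol: 18 per arm recruited, 15 per arm evaluable, quartile stratification, alpha 0.05, power 0.90, pre-post correlation rho = 0.50. Assumed, because the protocol does not give them: the t-test level (0.05, with 0.10 as a check), a group-by-time contrast, and the effect size. The interaction reading favours the plan: with main effects only, simulated power was about 0.44 with 15 per arm.

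**1. The plan's own figure.** No numerical effect is stated, so 15 per arm cannot be reproduced forwards. Solving backwards for 0.90 power with the repeated-measures interaction F test gives f of about 0.307. The noncentrality is f² × N × m / (1 − rho) = 0.307² × 30 × 2 / 0.5 = 11.3. This corresponds to a difference in change of 4 × 0.307 = 1.23 SD.

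**2. Does the switch fire for peak VO2?** Simulated allocation of 36 women, 40,000 runs:

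| Allocation | p < 0.05 | p < 0.10 |
|---|---|---|
| Unstratified | 4.9% | 10.1% |
| Within VO2 quartiles | 0 | 0.025% |

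Totals of 12 to 32 women and a skewed distribution also gave 0 at p < 0.05. After random loss of three per arm the rate was about 0.1%.

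**3. Variance by formula.** In units of the outcome variance, the change contrast has 2(1 − rho) = 1.00 at rho = 0.50, and ANCOVA has 1 − rho² = 0.75. ANCOVA's nominal saving is therefore (1 − rho)/2: 25% at 0.5, 15% at 0.7, 10% at 0.8. These formulas assume unstratified allocation.

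**4. Variance with stratification, 18 per arm.** The change model's nominal variance is (2/18) × 1.00 = 0.111, but the simulated sampling variance of the estimate was 0.090. For ANCOVA the two agree: (2/18) × 0.75 = 0.083 and 0.083. The estimates themselves differ by 1 − 0.083/0.090, about 8%. The rest of the gap is a default standard error that is too large by a factor of √(0.111/0.090) = 1.11.

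**5. Error rate and power with stratification, rho = 0.50, effect about 1.23 SD (8,000 runs each).**

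| Complete cases | Type I, plan's rule | Type I, ANCOVA | Power, plan's rule | Power, ANCOVA |
|---|---|---|---|---|
| 18 per arm | 0.031 | 0.050 | 0.960 | 0.983 |
| 15 per arm | 0.032 | 0.049 | 0.919 | 0.961 |

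The gain is 2.3 and 4.2 points. At rho = 0.7 with 15 per arm, power is 0.988 against 0.993. At rho = 0.8 both are practically 1 for this effect.

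**6. Outcomes unrelated to VO2 (no effective stratification), 15 per arm, effect 0.8 SD.** The switch fires in about 5% of trials. Power of the two-stage rule against ANCOVA always is about 0.57 against 0.67 at rho = 0.50, and 0.91 against 0.93 at rho = 0.8. The overall type I error of the two-stage rule at rho = 0.50 was 0.044 to 0.046.

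**The case against.** The strongest defence is that the primary test is valid and already meets its target. With stratification the default model has power of 0.92 with 15 per arm, above the planned 0.90, and it errs on the conservative side. That stands, and it limits how serious the point is.

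Several stronger readings are tempting but not supported:

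- **That baseline VO2 is discarded.** It enters the mixed model as the pre value. The change contrast has the same variance as a post-only comparison only at rho = 0.50, which is a planning assumption.
- **That the loss equals 33% more participants (1.00/0.75), or power of 0.90 against 0.96.** Those figures use the unstratified variances in step 3. Stratification already delivers most of that precision, and the estimates differ by about 8% in true variance.
- **That chance imbalance is left uncorrected.** The change contrast subtracts baseline in full. When baseline p lies between 0.05 and 0.20, it is falsely significant about 8 to 10% of the time at rho = 0.50. The cause is over-correction through regression to the mean.
- **That the rule inflates false positives.** The 8 to 10% applies to a selected slice of trials. Overall the rate is below 0.05.

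It is also fair to say that the protocol speaks of differences, not of significant ones. Significance is the natural reading, because the t-test is named in the sentence before. If it is not meant, the trigger is undefined.

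**Conclusion.** The point holds as a should-fix. The plan ties baseline adjustment to a test that its own stratification disables for the primary outcome. The result is a valid but conservative test (type I error about 0.03) and a loss of about 2 points of power with 18 per arm complete, or about 4 with 15.

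This rests on rho = 0.50, a group-by-time contrast, a 0.05 trigger and an effect of about 1.23 SD that the protocol does not state. At that effect both tests are close to full power, which itself limits the gain. A higher correlation shrinks it further: at rho = 0.8 it is at most about 1 to 2 points, as the 0.8 SD case shows.

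For outcomes unrelated to VO2, the loss at rho = 0.50 and 0.8 SD is about 10 points, falling to about 2 at rho = 0.8. There the choice of model rests on chance. The documents do not support a claim that the primary conclusion would be unsafe.

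**What to change.** - Delete the baseline t-tests and the conditional rule.
- For peak VO2, pre-specify an ANCOVA of the week-16 value on arm with baseline peak VO2 as a continuous covariate, whatever baseline difference is observed. An equivalent choice is a mixed model with a group-by-time term and a common baseline mean.
- Use the same model for other continuous outcomes measured only before and after. Drop the participant random factor where there is one post value.
- For outcomes measured more than once after baseline (accelerometry at weeks 8 and 16, the two-weekly activity questionnaire), keep the mixed model with its participant random effect. Add the outcome's own baseline as a covariate, or constrain the baseline means to be equal. A single week-16 ANCOVA would discard the intermediate data.

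The cost is a change of wording, best made before group allocation is unblinded. Baseline values are already collected, so no extra visits, measurements or participants are needed.

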## Discussion

Over the past two decades, growing scientific evidence has provided support for the efficacy of exercise to improve cancer-related health outcomes. Exercise is a beneficial adjunct therapy for improving treatment tolerance [73, 97, 98] and helps to mitigate patient’s symptom-reported end points as fatigue, pain, and depression [8, 30, 32–34, 44, 45, 50, 62, 99]. However, adoption and adherence to exercise programs among cancer survivors is low [53, 61, 66, 100]. Reasons for a lack of regular exercise among people living with and beyond cancer are multifactorial and involve social and demographic issues (i.e., cost, lack of facilities tailored for cancer survivors near home, age, socioeconomic and educational level), long-term effects of the cancer therapy (i.e., fatigue, compromised immune system, physical deconditioning), lack of motivation and discipline for individualized exercise programs, and a lack of recommendation by oncologists and other health professionals [21, 46, 50, 52, 63, 69].

The present trial will determine whether a supervised group exercise intervention combined to active lifestyle recommendations is a feasible option for breast cancer survivors. We expect that supervised exercise and social interaction offered by the group training sessions will be powerful strategies to improve exercise adherence, fitness, and socialization, offering an opportunity to participants to share experiences and enjoy mutual health-related improvements. We anticipate the supervised exercise group will present superior health, physical functioning, and quality of life indices after the intervention compared to the group receiving physical activity recommendations alone. The improvements we expect participants to experience following the supervised group-based exercise intervention may inspire participants to adhere to a long-term active lifestyle. The outcomes of this manuscript will be reported accordingly to the CONSORT guidelines (Fig. 4).

**Fig. 4 Fig4:**
[figure not shown]
Consolidated Standards of Reporting Trials (CONSORT) flow diagram summarizing the trial status

Prior to commencing the main trial, we conducted a small-scale pilot study to examine potential barriers to recruitment and the feasibility of protocol delivery. From this study, we learned that most of the participants in the unsupervised physical activity recommendations group did not answer phone calls during the intervention. Likewise, we acknowledge that some participants of this study neither did not have access to the ICESP booklet nor remembered to follow it, even though it is commonly used as a guideline by the Cancer Institute. Thus, to minimize these issues, we amended the protocol to include a standard talk about the benefits of physical activity for people living with cancer, immediately after the randomization. Furthermore, following the pilot study, we included the assessment of physical activity via accelerometry at the mid-intervention point (week 8), to provide a greater insight into change in physical activity behavior during the intervention. These procedures are meant to promote retention and complete follow-up of the participants.

Recruitment for the main trail has now commenced, and barriers identified to date include participants not found or not willing to take part, distance from the canoe training center (too far to travel), limitations imposed by the conventional therapy, movement restriction, and clinical clearance, among others. In addition, some barriers are observed once participants are recruited to the intervention, including requirement for mammary reconstruction surgery and distance from the canoe training center, which impact participants’ attendance to supervised exercise sessions. Regarding these barriers, the study staff will use all plausible means to overcome the limitations and support willing participants to continue in the study.

It is worth mentioning that after finishing the intervention period and concluding the assessments, all participants from both groups are advised to continue following an active lifestyle. As an encouragement, they are invited to enroll a Dragon Boat group training program offered at the Olympic Lane of Sports Center of the University of Sao Paulo at no cost. This is an integrated multidisciplinary program and partnership among ICESP, the Sports Center (Olympic Lane), and the School of Physical Education and Sport of the University of Sao Paulo. Cancer Institute’s physiatrists and oncology clinicians make triage and referrals, as well as nurses and physical therapists give advice and booklet recommendations for an active lifestyle. At the University of São Paulo’s Olympic Lane, participants exercise under supervision of physical education professionals and students. We assure that sustainable increase in exercise among cancer survivors relies on a qualified and collaborative multidisciplinary team that recognizes exercise as a safe and efficacious complementary therapy on cancer survivorship.

Our results will generate a body of evidence with the potential to advance knowledge on the impact of a supervised group exercise intervention to improve aspects related to health- and mental-related quality of life in female breast cancer survivors.

## Trial status

Recruitment began in June 2018. Initially, we would expect to conclude participants’ recruitment by July 2021. However, because of the current pandemic, recruitment should be delayed. This is version 3 of the protocol. Version 1 was submitted to the Research Ethics Committee of the USP School of Physical Education and Sports on November 2017; Version 2 included the ICESP as a co-participant institution and changed the age interval inclusion criteria from 45–75 to 35–75 years. Changes in version 3 were the exclusion of pain as an outcome (and the questionnaire to assess it), removal of obesity from the exclusion criteria, and the ones after the pilot study described in the “Discussion”.

## Abbreviations

ANCOVA: Analysis of covariance
BMI: Body mass index
CHOD/PAP: Cholesterol oxidase phenol 4-aminoantipyrine peroxidase
CONSORT: Consolidated Standards of Reporting Trials
DMSO: Dimethylsulphoxide
ELISpot: Enzyme-linked immunospot
EORTC QLQ-C30: European Organization for Research and Treatment for Cancer Quality of Life Questionnaire-Core
FBS: Fetal bovine serum
GPO-PAP: Glycerol phosphate oxidase peroxidase amidopyrine
H: Height
HDL: High-density lipoprotein
HPLC: High-performance liquid chromatography
ID-MS: Isotope Dilution-Mass Spectrometry
IMPRAF-54: Inventory of Motivation to the Regular Practice of Physical Activity
IFN-γ: Interferon Gamma
K_2_EDTA: Dipotassium Ethylenediaminetetraacetic Acid
LDL: Low-density lipoprotein
PBMCs: Peripheral blood mononuclear cells
R-PFS: Piper Fatigue Scale-Revised
RPMI: Roswell Park Memorial Institute media
SF-36: 36-Item Short-Form Health Survey
SPIRIT: Standard Protocol Items: Recommendations for Interventional Trials
UV: Ultraviolet
VM: Vector magnitude
VO_2_: Oxygen consumption
W: Weight
WHO: World Health Organization
